### Follow-up

Follow-up is planned at month 1, 3 and 6 following treatment completion, 6-monthly thereafter until month 24 and then yearly up to month 60. Patients who withdraw from trial treatment in the absence of progression should continue to have follow-up visits as defined above. The following investigations should be performed at every follow-up visit (Table 1):
Clinical examination with late toxicity scoringPSA and testosterone measurementQoL-scoringPET-imaging only at time of biochemical progression or symptomatic progression and then 6-monthly thereafter until clinical progression is determined. In case of biochemical progression, the PSA should at least be 0.50 ng/mL before a new PET-CT scan should be considered. The location of progression should be recorded.At time of primary endpoint is reached, a new biomarker sampling is preferred, but optional.Concomitant medicationSurvival status

In case of clinical disease progression the patient will be treated according to each centre policy, but adherence to the EAU guidelines [24] is recommended. In case of local or regional oligometastatic recurrence during follow-up, a new MDT is allowed (this treatment falls outside the scope of this protocol).

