### Objectives

#### Primary endpoint

MFS: time between randomization and the appearance of a metastatic recurrence (any M1) as suggested by choline, FACBC or PSMA PET-CT/PET-MRI or death due to any cause. In case of biochemical progression, restaging will be performed, preferably with the same PET-tracer. In case of negative PET findings at biochemical relapse, repeated PET imaging should be performed on a 6-monthly basis or earlier if clinically indicated.

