#### Secondary endpoints

Clinical PFS: time between randomization and the appearance of a new recurrence (any N1 or M1) as suggested by PET-CT or PET-MRI, symptoms related to progressive PCa or death due to any cause.Local recurrence: evidence of a recurrence on imaging inside the surgical or radiotherapy field. Confirmation per biopsy is recommended. For radiotherapy schedules, local response and local progression is defined as per RECIST 1.1 criteria.Regional nodal recurrence: radiographic evidence (PET-CT or -MRI) of lymphadenopathy in the pelvis, outside the surgical or radiotherapy field. Histologic confirmation is recommended, especially in the absence of biochemical recurrence.Distant recurrence: appearance of distant metastases (M1a, M1b, M1c) outside the pelvis evidenced by PET-CT or -MRI.Biochemical PFS: time between randomization and the day of the first recorded biochemical progression (as defined below), clinical progression or death due to clinical progression.RP at diagnosis: biochemical recurrence = PSA > 0.20 ng/mL, confirmed 2 weeks later.Prostate radiotherapy at diagnosis: biochemical recurrence = PSA nadir + 2 ng/mL (Phoenix definition).Patients whose PSA does not drop below 0.20 ng/mL (if previous RP) or below the level before treatment (if previous prostate radiotherapy) at time of first response assessment at 3 months follow-up, are considered as non-responders to treatment and are considered to have a biochemical recurrence in case a second measurement at least 2 weeks later confirms a stable or rising PSA above this level.Time to start of hormonal treatment: time from trial randomization to start of hormonal treatment.Time to castration-resistant disease: time from trial randomization until castration resistant status as defined in the EAU-guidelines [1].PCa-specific survival: time from trial randomization until death due to PCa.Overall survival (OS): time from trial randomization until death from any cause.Acute and late toxicity due to radiotherapy will be assessed according to the National Cancer Institute Common Terminology Criteria for Adverse Events (CTCAE) version 4.0 [20], with special attention for rectal, gastro-intestinal and urinary adverse events. Surgery related morbidity, e.g. intra-operative complications (blood loss, injury to other pelvic organs …), and post-operative surgical complications will be scored using the Clavien-Dindo Classification of Surgical Complications [21].Acute toxicity: occurring during and up to 3 months after treatment completion.Late toxicity: occurring later than 3 months after treatment completion.Quality of life (QoL) scoring using the EORTC QLQ-C30 supplemented with QLQ-PR25. Raw scores will be transformed to a linear scale ranging from 0 to 100 according to the EORTC manual. The multi-item scales of the QLQ PR-25 will be analysed at both the individual item and the scale level. The results will be presented in accordance with recent guidelines for reporting health related QoL randomized controlled trials [22].Pattern of progression.Sensitivity/specificity of PET-imaging for the detection of nodal recurrences: limited to patients undergoing surgery.Biomarker discovery: to develop a miRNA panel predictive for treatment response using whole genome miRNA expression profiling [23].

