**Quality of life**										
QLQ-C30		x						x	x	x
QLQ-PR25		x						x	x	x
**Survival status**							x	x	x	x

(a) All arms should receive an LHRH-agonist or antagonist for a duration of 6 months using 1 monthly formulations. In case of SBRT/WPRT, ADT should start no later than the first fraction (whichever RT treatment comes first) and no earlier than 2 weeks before the start of radiotherapy. In case of sLND, ADT should be started no earlier than 1 day postoperatively and no later than 10 days postoperatively

(b) Treatment should start preferably within 4 weeks after randomization, but no later than 8 weeks after randomization. Treatment period is defined as the time between first treatment day and last treatment of surgery and/or radiotherapy

(c) Physical examination including scoring of Performance Status. Weight and height will only be measured at screening

(d) Whole body choline, PSMA or FACBC PET-CT/−MRI. During follow-up repeat PET-CT only at time of biochemical relapse and then 6-monthly afterwards until clinical progression is determined or earlier in case of symptomatic progression

(e) Optional: for patients without a prior radical prostatectomy it is recommended to perform a multiparametric MRI of the prostate to rule out local recurrence

(f) During the treatment period a toxicity assessment should be done at least once a week in case of WPRT. For SBRT toxicity assessment should be done only at end of treatment, for sLND at discharge (Clavien-Dindo scale)

(g) 6-monthly follow-up for a minimum of 24 months, with yearly follow-up thereafter up to 60 months or until progression. In case of clinical progression, the patient will be treated according to the EAU guidelines

(h) In case of SBRT/WPRT, PSA has to be determined on the day of the last fraction. In case of sLND in arm A, PSA will be determined at 4 weeks after surgery (follow-up month 1). In case of sLND + WPRT in arm B, PSA will be determined at 4 weeks post-WPRT (follow-up month 1)

(i) At time of primary endpoint is reached, a new biomarker sampling is preferred, but optional

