SBRT (MDT):A total dose of 30 Gy (80% of the maximal dose) will be delivered in 3 fractions and fractions will be separated > 48 h and < 96 h. Treatment will be prescribed to the periphery of the target (80% of the dose (= 30 Gy), should cover 90% of the PTV). In case of violation of dose constraints to the surrounding OAR, the prescription will be adapted accordingly.

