#### Surgery – sLND (MDT)

A bilateral extended lymph node dissection of the true pelvis will be performed either via an open or minimally invasive approach, which is at the discretion and expertise of the surgeon. A minimally invasive technique is preferred, but not mandatory. In case of pelvic nodal uptake, all nodal/fibrofatty tissue at the external and internal iliac regions and obturator fossa region will be removed. For pelvic nodal metastases, in case of a previous extended lymphadenectomy, only the suspicious lymph node(s) will be removed. The definition of the true pelvis is defined according to the AJCC Cancer Staging Manual 7th edition and the regions are defined by Mattei et al. [33]. An extended lymph node dissection of regions I and II is recommended in this study.

In case of WPRT after sLND in arm B: WPRT should start between the 4th and 12th week following sLND. In case the morbidity of sLND does not allow a safe start of RT in this period, radiotherapy will not be carried out.

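### MFS and PFS run from randomisation but PSA visits run from the end of local treatment, so in men without prostate-bed radiotherapy arm A is assessed first and the log-rank test tilts modestly toward arm B

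*Protocol article*

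**What the plan says.** All three time-to-event endpoints at issue share one origin. Under Primary endpoint: "MFS: time between randomization and the appearance of a metastatic recurrence", or death from any cause. Under Secondary endpoints, clinical PFS also runs from randomisation, and so does the biochemical endpoint: "Biochemical PFS: time between randomization and the day of the first recorded biochemical progression".

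The visit calendar has a different origin. Under Follow-up: "Follow-up is planned at month 1, 3 and 6 following treatment completion, 6-monthly thereafter until month 24 and then yearly up to month 60". Table 1, note (b), fixes what completion means: "Treatment period is defined as the time between first treatment day and last treatment of surgery and/or radiotherapy". ADT is therefore not counted. Note (h) confirms that the anchor depends on the arm: after sLND, the month-1 PSA is taken 4 weeks after surgery in arm A but 4 weeks after WPRT in arm B.

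PET is not done at every visit. It follows biochemical or symptomatic progression and is then repeated 6-monthly. The window for starting treatment (preferably 4 weeks, at most 8 weeks after randomisation) is the same in both arms, so it does not cancel a difference in treatment length. Nothing in the article ties the assessments to randomisation.

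**The concern.** An asymptomatic metastasis usually comes to light because a scheduled PSA prompts a PET scan. If the scheduled PSA falls at a later time since randomisation in one arm, the recorded event times depend on the calendar as well as on the disease. The log-rank test compares arms at each recorded event time. When arm A's visit comes first in each cycle, arm A's events are counted while arm B's comparable events are still undiscovered.

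The trial decides whether arm B goes on to phase III, at a two-sided alpha of 0.20, that is 0.10 in the direction of benefit. An artefact in the favourable direction makes an already permissive screen more permissive.

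There is a secondary consequence. The month-3 visit carries the PSA non-responder rule and QoL. Because it is counted from the end of local treatment, it can fall at a different point of the 6-month ADT course in the two arms.

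**Working it through.** **1. The plan's own sample size.** HR = 24/36 = 0.667, two-sided alpha 0.20, power 80%. Schoenfeld events = 4 × (1.2816 + 0.8416)² / (ln 0.667)² ≈ 110. With exponential MFS and 48 + 24 months, the event probability is 0.729 in arm A and 0.589 in arm B, mean 0.659. Then 110 / 0.659 = 166.9, and 166.9 / 0.95 = 176. Freedman's formula gives 113 events and 181 patients. The stated 178 lies between the two and is not in question.

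**2. Length of local treatment, first to last day.**
- SBRT: "will be delivered in 3 fractions and fractions will be separated > 48 h and < 96 h" (Radiotherapy section). Two gaps of 2 to 4 days give 4 to 8 days.
- WPRT: 25 fractions at 5 per week give 4 × 7 + 4 = 32 days.
- sLND then WPRT: "WPRT should start between the 4th and 12th week following sLND" (Surgery section). This gives 28 to 84 + 32 = 60 to 116 days, against the day of surgery alone in arm A.
- Prostate-bed radiotherapy: at least 33 fractions, 6 × 7 + 2 = 44 days.

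**3. Visit lag, arm B minus arm A.**

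| Stratum | Lag in days | Lag in weeks |
|---|---|---|
| SBRT, no prostate-bed RT | 32 − 8 to 32 − 4 = 24 to 28 | 3.4 to 4.0 |
| sLND, no prostate-bed RT | 60 to 116 | 8.6 to 16.6 |
| SBRT, prostate-bed RT combined in arm A | 44 − 44 = 0 | 0 |
| SBRT, prostate-bed RT after SBRT in arm A | at most 44 − (44 + 4) = −4 | −0.6 or lower |

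Arm B sLND men whose radiotherapy is not carried out have no lag. For prostate-bed radiotherapy after sLND in arm A the article gives no interval, so that lag cannot be computed.

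**4. Why order matters although the mean delay does not differ.** Take n men at risk per arm and a short lag, with d events found at arm A's visit and then d at arm B's. Observed minus expected events in arm B is −d/2 + d(n − d)/(2n − d) = −d²/[2(2n − d)]. With n = 178/2 = 89, median 24 months and a 6-month interval, d = 89 × (1 − 2^(−6/24)) = 14.2, and the result is −14.2²/(2 × 163.8) ≈ −0.6 events from one pair of visits. Each pair pushes the same way. This is the limiting case of a short lag and a common visit date within each arm; variable treatment start and visit windows dilute it. A longer lag also lengthens arm B's first interval and offsets part of the tilt, so the effect is largest in the SBRT stratum, where the lag is shorter.

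**5. Simulation under no effect.** 178 patients, median 24 months in both arms, 48 + 24 months, stratified log-rank, event dated at the next scheduled visit, censoring at cut-off. Treatment start was spread over 0 to 8 weeks with visits ±14 days, or over 0.5 to 1.5 months with exact visits. One set of runs had no events in the first 6 months. The sLND share was varied from 0 to 100%.

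| Setting | Chance of significance favouring arm B | Apparent HR |
|---|---|---|
| Visits counted from the same point in both arms | 0.09 to 0.11 | about 1.00 |
| As written, no prostate-bed RT | 0.12 to 0.17 | 0.94 to 0.98 |
| As written, 30 to 50% prostate-bed RT | about 0.11 to 0.14 | nearer 1 |

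Mean delay from true event to recorded date is 3.7 months in both arms under constant hazard. With no events in the first 6 months it is 4.2 months in arm A and 3.9 to 4.2 in arm B.

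Under the planned 24 against 36 months with 25% sLND and constant hazard, the HR moves from 0.67 to 0.63–0.65 and rejection from 78–79% to 83–85%.

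**6. Month-3 visit and ADT.** After sLND, this visit falls at about postoperative week 13 in arm A and week 22 to 30 in arm B (60 to 116 days + 91 days). ADT starts on postoperative day 1 to 10 and lasts 6 months, to about week 26 or 27. In the SBRT stratum the visit falls at about week 14 against week 18 from the first fraction, so both arms are still on ADT.

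**The case against.** The strongest reply is that the effect is small and rests on shares the article does not give. Prostate-bed radiotherapy is highly recommended for pT3a/b-4 or R1 disease or a PSA of at least 2 ng/mL, so it may be common, and in the SBRT stratum it removes or reverses the lag. Deaths and symptom-triggered PET do not follow the calendar. After biochemical relapse PET is repeated 6-monthly, and a first positive PET may show nodal disease that is not an MFS event. One simulation with 20% sLND, 30% prostate-bed radiotherapy, 15% of events found off schedule and PSA relapse 0 to 12 months before M1 gave 0.108 with HR 0.99; with 50% prostate-bed radiotherapy it gave 0.09 to 0.11, which is no visible inflation. All of this stands, and it limits the point to a modest one. It does not remove the arm-dependent calendar.

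Stronger readings are tempting, and the documents do not support them:
- That arm B is seen later at every visit. This fails for SBRT-stratum men with prostate-bed radiotherapy and for arm B sLND men whose radiotherapy is not carried out.
- That arm B events are dated 4 to 17 weeks later. An event falling between the two arms' visits is found sooner in arm B, and the mean delays are about equal. The full lag applies only where a given visit fixes the date, as in the 3-month PSA non-responder rule.
- That yearly visits cover both planned medians. Visits are 6-monthly to month 24; only the 36-month median lies in the yearly stretch.
- That the false-positive chance exceeds 0.20. Values of 0.17 to 0.22 and above need censoring at the last visit, which the article does not state.

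**Conclusion.** The point holds as a modest, avoidable bias in the primary comparison. Endpoint clock and visit clock have different origins, and the gap depends on the arm: about 4 weeks in the SBRT stratum and 9 to 17 weeks in the sLND stratum for men without prostate-bed radiotherapy. The direction favours arm B. The inflation is about 2 to 7 percentage points on a nominal 10% tail without prostate-bed radiotherapy and about 1 to 4 points with a 30 to 50% share; it may vanish if that share is high and many events are found off schedule.

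The lags follow from the article's own figures. The error rates rest on assumed sLND and prostate-bed shares, assumed spread of treatment start, and events dated at the next scheduled visit. The difference in ADT phase at month 3 is clear only for late-starting WPRT after sLND; visits in weeks 22 to 26 are still on ADT.

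**What to change.** - Count the endpoint PSA and QoL visits from month 6 onward from randomisation in both arms: months 6, 12, 18 and 24, then the planned spacing.
- Keep the month 1 and month 3 post-treatment visits for acute toxicity and for the 3-month PSA response rule. Moving month 3 to randomisation would not work: treatment may start up to 8 weeks after randomisation and WPRT up to 12 weeks after sLND, so the visit could precede or fall within WPRT. At month 6 this is an edge case: the latest completion is 56 + 116 = 172 days without prostate-bed radiotherapy and 56 + 84 + 44 = 184 days with 33 fractions.
- Add an interval-censored MFS analysis, from last negative to first positive assessment, as a sensitivity analysis. It also covers men already enrolled, whose visit dates cannot be changed.

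The lag in the 3-month non-responder rule remains for biochemical PFS and should be acknowledged when that endpoint is reported.

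The cost is an amendment to the visit calendar and eCRF windows and a little more analysis. No treatment changes, and the sample size stays at 178.

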A recent systematic review showed that most published series on MDT are small with heterogeneous patient populations, making it difficult to make treatment recommendations [5, 7, 8]. To address these shortcomings, an international patient database on oligometastatic PCa recurrence (≤3 lesions) was established allowing to study a homogeneous patient population treated with stereotactic body radiotherapy (SBRT) [10]. A first analysis of this series showed that the majority of patients treated with SBRT for nodal recurrence, relapse within 2 years in nearby lymph node regions, with an estimated median time to progression of 12–18 months [11–13]. Similar results in terms of time to progression were observed in a large multi-institutional study exploring the role of salvage lymph node dissection (sLND) after nodal recurrence [14]. These comparable results could probably be explained by a lack of sufficient sensitivity of the current imaging techniques to perform a lesion-based approach, either by SBRT or sLND. An elective nodal irradiation approach using whole pelvic radiotherapy (WPRT) in addition to MDT could delay or even prevent such relapse [12, 15–17]. Improved progression-free survival (PFS) rates have been observed with WPRT in radiotherapy series [15–17], as well as after sLND as demonstrated in the retrospective study by Rischke et al. [12].

The current trial wants to explore the potential benefit in terms of metastasis-free survival (MFS) of an elective nodal approach by adding WPRT to either sLND or as alternative to focal SBRT. The proposed trial randomizes patients with oligorecurrent nodal PCa following primary PCa treatment to either MDT (sLND or SBRT) or WPRT plus MDT (focal radiotherapy boost or sLND). As two recent trials have suggested a progression-free and even overall survival benefit by adding temporary ADT to local therapy in case of biochemical recurrence [18, 19], a positive effect could also be expected for regional recurrence. Although the optimal duration of ADT is unknown, a minimal duration of 6 months of ADT seems advisable in this setting and is mandatory for both arms.

This trial will improve our insights in the pattern of recurrence following these treatment modalities with the expectation that WPRT will reduce the number of nodal relapses, improving MFS and postponing the need for palliative systemic treatment while maintaining quality of life (QoL).

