Although sLND is not a pure lesion-directed approach, the recurrence patterns of both SBRT and sLND are comparable with > 60% of patients relapsing in adjacent lymph node regions [11–13]. This might be explained by the fact that even the most extended sLND does not cover all potential pelvic lymph node metastasis landing sites. In a previous paper from our group, we indicated that an extended sLND technique only covers around 50% of these sites [41]. Consequently, we hypothesize that a larger RT field covering the elective nodal regions in a treatment field may be a more effective alternative to focal strategies. This is supported by a retrospective study by Rischke et al. [12], indicating a reduced pelvic lymph node recurrence rate following sLND plus WPRT as compared to sLND alone. On the other hand, compared to MDT strategies, longer OTT, higher toxicity rates and limited re-treatment possibilities are expected by delivering elective nodal irradiation. Nevertheless, WPRT grade 3 toxicity rates appear to be low in recent trials such as OLIGOPELVIS and SPPORT [42, 43].

In both arms, short term ADT will be mandatory. The rationale for the use of temporary ADT is extrapolated from the data in the salvage setting (GETUG16, RTOG9601, SPPORT, OLIGOPELVIS), indicating that temporary ADT reduces the rate of biochemical and clinical recurrences [12, 18, 19, 42, 43]. There are no clear guidelines on the ideal duration of ADT in this setting, so we opted for 6 months as studied in GETUG16, OLIGOPELVIS and SPPORT [19, 42, 43].

As no direct comparison of the two approaches have been made to date, prospective studies using well-defined endpoints and predefined treatment approaches are therefore needed to validate the best treatment approach in the nodal oligorecurrent setting. The STORM study will be the first prospective multicentre randomized controlled phase II trial to assess the possibility of prolonging the MFS by adding WPRT to either sLND or SBRT, both in combination with short-term ADT in PCa patients with nodal oligorecurrent disease.

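### Scheduled PET stops at clinical progression, which includes a pelvic N1 relapse, although the primary endpoint is M1 or death; later M1 is not systematically ascertained, and the gap probably falls more on arm A

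*Protocol article*

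**What the plan says.** - **Primary endpoint.** MFS runs from randomization to "the appearance of a metastatic recurrence (any M1) as suggested by choline, FACBC or PSMA PET-CT/PET-MRI or death due to any cause". A pelvic nodal relapse is not an event. The same section sets a repeat-scan rule, but only for one situation: "In case of negative PET findings at biochemical relapse, repeated PET imaging should be performed on a 6-monthly basis or earlier if clinically indicated". It is silent on a scan that is positive for N1 and negative for M1.
- **Secondary endpoints.** Clinical progression-free survival counts "the appearance of a new recurrence (any N1 or M1) as suggested by PET-CT or PET-MRI", as well as symptoms or death. N1 alone is therefore clinical progression.
- **Follow-up.** PET is done "only at time of biochemical progression or symptomatic progression and then 6-monthly thereafter until clinical progression is determined". Table 1 note (d) repeats the rule: after the first scan at biochemical relapse, "then 6-monthly afterwards until clinical progression is determined or earlier in case of symptomatic progression".
- **Visits.** The Follow-up text plans visits to month 60, with PSA and survival status, and names no stop at progression. Table 1 note (g) stops them at month 60 or at progression, without saying which kind.
- **After regional relapse.** A new MDT is allowed, outside the scope of the protocol.
- **Hypothesis.** The Background expects that "WPRT will reduce the number of nodal relapses, improving MFS". The Discussion describes recurrence patterns after SBRT and sLND as "comparable with > 60% of patients relapsing in adjacent lymph node regions".

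**The concern.** The imaging rule suits clinical progression-free survival, a secondary endpoint, and not MFS. A site that follows it stops scheduled imaging when a man has a pelvic-only relapse, although he is still at risk of the primary event. That relapse is also the event WPRT is meant to prevent. If WPRT works as expected, more arm A men reach the point where scheduled M1 ascertainment ends. Metastases that arise after N1 would then be under-recorded mainly in arm A, and the part of the benefit that runs through prevented nodal relapse would be partly removed from the comparison. The sample size allows 5% loss to follow-up and nothing for this. An analysis plan cannot recover M1 dates that were never collected.

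**Working it through.** **1. The planned sample size, which assumes MFS is observed to study end.** Inputs from Sample size: medians 24 and 36 months, two-sided alpha 0.20, power 80%, accrual 48 months plus 24, 5% loss, N = 178.
- Events (Schoenfeld): 4(1.2816 + 0.8416)² / ln(24/36)² = 109.7, so 110.
- Event probability with exponential times: 1 − (e^(−24λ) − e^(−72λ))/(48λ), which is 0.729 in arm A and 0.589 in arm B, mean 0.659.
- 110/0.659 = 167; 167/0.95 = 176. Capping each man at 60 months gives 178. The stated figure reproduces.

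**2. Loss of events alone.** 178 × 0.95 × 0.659 is about 111 events, power 80.5%. Let a fraction f of events be missed while the hazard ratio (HR) stays at 0.667. The document does not give f, so a range is shown.

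| f | Events | Power |
|---|---|---|
| 10% | 100 | 77% |
| 20% | 89 | 74% |
| 30% | 78 | 69% |
| 40% | 67 | 65% |
| 50% | 56 | 59% |

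This leaves out any bias in the HR.

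**3. Loss that depends on N1: an illustration.** Assumptions:
- Median first progression in arm A is 15 months, the middle of the 12–18 months in the Background. Total rate λ = ln2/15 = 0.0462 per month.
- 60% of first relapses are pelvic-only (assumed). N1 rate a = 0.0277; direct M1 rate d = 0.0185.
- The rate μ from N1 to M1 is set so that arm A median MFS is 24 months: e^(−24λ) + a(e^(−24μ) − e^(−24λ))/(λ − μ) = 0.5 gives μ of about 0.068.
- WPRT halves a and changes nothing else. No other loss; follow-up uniform between 24 and 72 months.
- After N1, a random share of men (the capture share) has later M1 recorded. The rest are treated as censored at N1.

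| Capture share | HR | Events per 178 |
|---|---|---|
| 100% | 0.81 | 131 |
| 50% | 0.85 | 101 |
| 0% | 0.99 | 70 |

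The zero-capture row can be checked by hand. Only direct M1 counts, with the same rate d in both arms, so the HR is 1 apart from simulation error. Expected events are 89 × (d/total rate) × P(first progression within follow-up):
- Arm A: 89 × 0.40 × 0.867 = 31.
- Arm B: total rate 0.0139 + 0.0185 = 0.0323, so 89 × 0.571 × 0.766 = 39.
- Together 70.

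**4. Handling matters too.** If men were carried as event-free after N1 with no later M1 recorded, the same model over 12–18 months' median first progression gives an HR of 1.28–1.37. Both ways of handling unrecorded M1 work against WPRT in this model.

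**The case against.** A reader might infer that MFS is censored at N1 and goes unobserved afterwards. The document does not say that. No section gives a censoring rule for MFS, Data analysis says only that men are analysed as assigned, and a separate analysis plan may set the rule. Observation also continues in several ways:
- The Follow-up text keeps visits with PSA and survival status to month 60.
- Deaths are MFS events, and overall survival needs them.
- M1 seen on the same scan as N1 is captured.
- Time to castration resistance and time to hormonal treatment need follow-up past N1.
- The ADT section allows repeat MDT and links palliative ADT to symptoms or conventional imaging, so later imaging is foreseen.
- The stopping phrase may have been meant only to close the search in men with a rising PSA and a negative PET.

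A reader might also take the share above 60% in the Discussion to mean that more than half of the MFS events would be lost. That figure is the share of men relapsing in adjacent nodal regions. It is neither the share of first relapses that are pelvic-only nor the share of M1 events preceded by N1.

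These points stand and limit the size of the problem. They leave the gap in place: no scan is scheduled after an N1-only relapse, note (g) and the Follow-up text disagree on visits, and unscheduled imaging in an open-label trial may differ by site and by arm. Nor does the month-60 plan settle the matter, because its instruction to keep following men who withdraw from treatment covers only those without progression.

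**Conclusion.** The concern holds in this form: after an N1-only relapse, later M1 is not systematically ascertained for an endpoint that consists of M1 or death, and the visit rules conflict. By the trial's own hypothesis the gap falls more often on arm A, so it risks informative loss of MFS events and a bias that hides a WPRT benefit. If WPRT did not change the N1 rate, the loss would be roughly balanced and would mainly cost power.

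The size cannot be fixed from the document. In the illustration the HR moves only from about 0.81 to 0.85 when half of the post-N1 course is captured, but events fall from 131 to 101. The disappearance of the effect (0.99, 70 events) requires that no M1 is found after N1, and the document does not support assuming that. These figures rest on the assumed 60% pelvic-only share, the 15-month median, constant rates, random capture and an effect of WPRT on N1 only.

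**What to change.** 1. In Follow-up and in Table 1 notes (d) and (g), state that N1 or local relapse does not end primary-endpoint follow-up, which runs to M1, death or end of study.
2. Reconcile note (g) with the Follow-up text so that visits with PSA and survival status continue to month 60 after N1.
3. Record the date and M status of every later restaging scan done in routine care, and the type and date of any salvage treatment.
4. State that MFS is not censored at N1 or at salvage MDT.

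Items 3 and 4 belong together: carrying men forward without recording their M status would add bias, as step 4 of the working shows. No additional PET should be mandated.

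The cost is protocol wording, an eCRF form and longer data collection for men with progression. The remaining weakness is that M1 dates after N1 will depend on when routine imaging is done.
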